**Figure 3 fig3:**
[figure not shown]
Schematic diagram of rTMS targeting the primary motor cortex (M1 area). L M1 represents the left primary motor cortex, R M1 represents the right primary motor cortex. The M1 area is the core region of the brain responsible for regulating body movements. CZ is the standard electrode position in scalp electroencephalography (central zero point), located on the midline of the scalp, approximately corresponding to the central area of the top of the head, and can be used as one of the anatomical reference landmarks for locating the M1 area.

#### Control group 1: conventional acupuncture (CA) + rTMS

Conventional acupuncture acupoints are as follows:

Jianyu (LI 15), Jianliao (SJ 14), Jianzhen (SI 9), Naoshu (SI 10), Bingfeng (SI 12), Tianzong (SI 11), Quyuan (SI 13), Jianwaishu (SI 14), Jianzhongshu (SI 15), Quchi (LI 11), Waiguan (SJ 5), and Hegu (LI 4). The locations are detailed in Table 3 and Figure 4.

**Table 3 tab3:** Acupoint localization for conventional acupuncture.

Acupoint name	Code	Meridian	Anatomical localization (WHO standard)
Jianyu	LI 15	Large intestine	On the shoulder, anterior and inferior to the acromion, in the depression formed when the arm is abducted to the horizontal position.
Jianliao	SJ 14	Triple energizer	On the shoulder, posterior to the acromion, in the depression about 1 cun posterior to LI15, midway between LI15 and SI9.
Jianzhen	SI 9	Small intestine	On the posterior shoulder, 1 cun superior to the posterior axillary fold when the arm is adducted, in the depression inferior to the scapular spine.
Naoshu	SI 10	Small intestine	On the scapula, in the depression superior to the posterior axillary fold, directly above SI9 at the level of the axillary crease.
Tianzong	SI 11	Small intestine	In the center of the supraspinous fossa of the scapula, directly superior to SI11, midway between SI10 and SI13.
Bingfeng	SI 12	Small intestine	In the center of the infraspinous fossa of the scapula, at the midpoint between the inferior border of the scapular spine and the inferior angle of the scapula.
Quyuan	SI 13	Small intestine	Medial to the scapular spine, at the midpoint between SI10 (Naoshu) and the spinous process of the 2nd thoracic vertebra (T2).
Jianwaishu	SI 14	Small intestine	On the back, 3 cun lateral to the lower border of the spinous process of the 1st thoracic vertebra (T1).
Jianzhongshu	SI 15	Small intestine	On the back, 2 cun lateral to the lower border of the spinous process of the 7th cervical vertebra (C7).
Quchi	LI 11	Large intestine	At the lateral end of the cubital crease, midway between LU5 (Chize) and the lateral epicondyle of the humerus, with the elbow flexed.
Waiguan	SJ 5	Triple energizer	On the forearm, 2 cun proximal to the dorsal wrist crease, between the radius and ulna.
Hegu	LI 4	Large intestine	On the dorsum of the hand, between the 1st and 2nd metacarpal bones, at the midpoint of the 2nd metacarpal bone on the radial side.

Acromion: Bony prominence at the lateral end of the scapular spine; Supraspinous: Depression above the scapular spine; Infraspinous: Depression below the scapular spine; cun: Relative measurement based on the patient’s anatomy (e.g., the width of the thumb at the interphalangeal joint = 1 cun); C7: Most prominent cervical spinous process when neck is flexed; T1/T2: First/s thoracic vertebrae below C7.

**Figure 4 fig4:**
[figure not shown]
Acupoint illustration for conventional acupuncture.

#### Acupuncture technique

Identical needles (0.30 mm × 40 mm) will be used for acupuncture. The insertion depth, manipulation to achieve deqi, deqi criterion, needle retention time (30 min), and treatment schedule (once daily, 20 sessions) will be standardized to match the procedures in the experimental group, leaving only the acupoint prescription as the major variable.

rTMS procedure:

The rTMS protocol (parameters, site, and schedule) is identical to that described for the experimental group.

#### Control group 2: sham acupuncture + rTMS

Acupuncture technique:

Acupoint selection: The same set of 12 acupoints used in the experimental group will be used for the control group.

Sham needling technique: The non-penetrating Streitberger-type placebo needle (Asiamed) will be applied at each acupoint (36, 37). This device has a blunt tip that retracts into the handle upon contact with the skin, allowing insertion without piercing the skin. The needle will be fixed in place with an adhesive ring to mimic the appearance of a real needle.

Simulated deqi: To maintain blinding, the acupuncturist will gently manipulate the sham needle handle periodically without applying penetrating pressure and will ask open-ended questions about sensation, not mentioning specific deqi sensations.

Needle retention: The sham needles will remain in place for 30 min, matching the retention time in the active acupuncture groups.

Treatment schedule: The session frequency and duration (once daily, 20 sessions) will be identical to the other groups.

rTMS Procedure:

The rTMS protocol (parameters, site, and schedule) will be identical to that described for the experimental group.

### Relevant concomitant care permitted or prohibited during the trial

#### Permitted concomitant care

Patients will be allowed to receive their regular medications for secondary stroke prevention, including antihypertensive drugs, lipid-lowering drugs, hypoglycemic drugs, antiplatelet drugs, and anticoagulants. The dosages of these drugs will remain stable for at least 4 weeks before randomization and shall remain unchanged throughout the entire trial. Celecoxib will be allowed for emergency pain relief, but the dosage, time, and reasons for its use will be recorded in the patient’s diary in a real-time manner. Routine physical therapy of the hemiplegic limb, including range-of-motion training and stretching exercises, will be allowed as long as it begins at least 1 month before enrollment; however, the frequency and intensity of the treatment will not increase in the trial.

#### Prohibited interventions

All pain management interventions beyond the allowed emergency pain relief interventions will be prohibited. This prohibition will cover opioids, neuromodulators (such as gabapentin and pregabalin), corticosteroids, and interventional pain management procedures (such as nerve blocks and spinal cord stimulation). In addition, new pain medications or adjustments to the dosage of existing pain medications will be prohibited. Furthermore, any experimental interventions, such as other forms of neuromodulation, transcranial direct current stimulation, acupuncture, transcutaneous electrical nerve stimulation, and experimental medications or devices, will be prohibited. Invasive interventions, including surgery and joint injections, will also be prohibited. Moreover, intensive rehabilitation interventions for the affected limb, such as constraint-induced movement therapy and robot training, will not be allowed.

#### Outcomes

The efficacy of the intervention will be evaluated by two independent research assistants blinded to group assignment, using pre-specified primary and secondary outcomes. Assessments will be conducted at baseline (before the first treatment), on days 10 and 20, and 1 and 3 months after the end of treatment (Table 4).

**Table 4 tab4:** Schedule of outcome assessments across study time points.

Item	Timepoint				
	Baseline	Treatment period		Follow-up period	
		10 day	20 day	1 month	3 month
Enrolment					
Screening	√				
Signed informed consent	√				
Randomization	√				
Intervention					
Yuan-Luo Da-Jie-Jing acupuncture + rTMS					
Conventional acupuncture + rTMS					
Sham acupuncture + rTMS					
Assessment					
Primary outcome					
VAS	√	√	√	√	√
Secondary outcome					
Brunnstrom	√	√	√	√	√
Modified ashworth	√	√	√	√	√
AROM	√	√	√	√	√
Simplified Fugl-Meyer	√	√	√	√	√
Improved Barthel index	√	√	√	√	√
Infrared thermal imaging	√	√	√	√	√
RS-fMRI	√	√	√	√	√
CRPS-specific severity	√	√	√	√	√
Other measures					
Blinding assessment		√	√	√	√
Additional treatment		√	√	√	√
Rescue medication use		√	√	√	√
Adverse event		√	√	√	√

VAS, Visual Analogue Scale; rTMS, Repetitive transcranial magnetic stimulation; AROM, active range of motion; RS-fMRI, Resting-state functional magnetic resonance imaging.

#### Baseline

The general condition of eligible participants, including demographic and clinical characteristics, such as age, weight, and disease treatment history, will be recorded in the CRF. The research assistants will conduct the primary and secondary outcomes assessment before the first session of treatment.

#### Primary outcome

Pain intensity will be regarded as the primary outcome. It will be assessed using the visual analogue scale (VAS). The VAS will range from 0 (no pain) to 10 (worst imaginable pain). A reduction of ≥1.5 points will be considered a clinically meaningful improvement (38). The analysis will focus on the mean change from baseline to each time point.

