#### Statistical methods

All statistical analyses will be conducted by an independent statistician blinded to group allocation. A two-sided significance level of *α* = 0.05 will be applied for all inferential tests.

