#### Primary outcome analysis

Pain intensity, measured based on the VAS, will be analyzed using a linear mixed-effects model (LMM). Fixed effects will include group, time, group-by-time interaction, baseline VAS score, and rescue medication use. Random effects will account for participant-specific intercepts. Between-group differences at each time point will be estimated with 95% confidence intervals (CIs). A reduction of ≥1.5 points from baseline will be considered clinically meaningful. Pre-planned contrasts will be conducted to test the following hypotheses: (1) the experimental group (YLDJJ + rTMS) will be superior to control group 2 (sham acupuncture + rTMS); and (2) the experimental group will be superior to control group 1 (conventional acupuncture + rTMS). These comparisons will directly test the specific efficacy of YLDJJ acupuncture with those of both a sham control and a conventional acupuncture active control.

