#### Software and reporting

All analyses will be conducted using R software (v4.5.0) and the packages lme4, mice, and geepack. All results will be reported as statistical estimates with 95% confidence intervals, along with effect sizes for statistically significant outcomes. The false discovery rate will be used for multiple comparison adjustment in secondary outcomes.

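### No primary time point and no decision rule for the two primary contrasts, so the error rate of the main pain claim is not held at 5%

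*Protocol article*

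**What the plan says.** Five places in the protocol article bear on this.

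- **Primary outcome.** VAS pain is primary, and "The analysis will focus on the mean change from baseline to each time point".
- **Outcomes and Table 4.** "Assessments will be conducted at baseline (before the first treatment), on days 10 and 20, and 1 and 3 months after the end of treatment". That makes four post-baseline VAS visits.
- **Primary outcome analysis.** From a linear mixed model, "Between-group differences at each time point will be estimated with 95% confidence intervals (CIs". Separately, "Pre-planned contrasts will be conducted to test the following hypotheses", and two are listed: the YLDJJ arm superior to the sham arm, and the YLDJJ arm superior to the conventional acupuncture arm. Neither hypothesis has a visit attached. No order, alpha split or joint-success rule is given.
- **Statistical methods.** A two-sided 0.05 level "will be applied for all inferential tests".
- **Software and reporting.** "The false discovery rate will be used for multiple comparison adjustment in secondary outcomes". No adjustment is stated for the primary outcome.

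Day 20 is singled out only in the per-protocol definitions (Exclusion from PP analysis; Analysis populations). The Sample size section names no visit.

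**The concern.** A primary outcome needs a measure, a time point and a rule for what counts as success. Here only the measure is fixed. The trial could be declared positive on day 20, at 3 months or at another visit, and against sham, against conventional acupuncture or against both. Each of these could be defended from the text after the data are seen. The 0.05 level would then describe each single test but not the trial's conclusion.

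The protocol is not merely silent here. It directs the primary analysis at every visit, sets 0.05 for all tests and places the adjustment with secondary outcomes. Data collection and management requires the analysis plan to be consistent with the protocol, so a consistent plan would inherit the gap.

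**Working it through.** **Inputs from the article.** Four post-baseline visits; two contrasts sharing the YLDJJ arm; 1:1:1 allocation; two-sided 0.05 per test; difference 1.5; SD 1.8; power 90%; 33 per group, raised to 42 for 20% dropout.

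**Assumption.** The correlation ρ of VAS between visits is not stated. The range 0.3–0.8 is used, with 0 and 0.9 also shown.

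**1. The plan's own figure.** d = 1.5/1.8 = 0.833. A two-sample t-test at 0.05 with 90% power needs 32 per group (31 by the normal formula), close to the stated 33. Then 33/0.8 = 41.25, rounded up to 42. The stated method, a three-group ANOVA with f = 0.42, gives 25 per group. The plan's 33 is thus in effect a pairwise calculation, and the power figures below are pairwise. With 33 completers per group, pairwise power is 91.5% at 0.05.

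**2. Two contrasts at one visit.** With equal arms, each contrast has variance 2σ²/n and the two share covariance σ²/n through the YLDJJ arm, so their correlation is 0.5. The chance that at least one |Z| exceeds 1.96 under the null is 9.1%. Treating the tests as independent would give 1 − 0.95² = 9.75%. This figure needs no assumption about ρ.

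**3. Two contrasts at four visits.** The correlation between two test statistics is the contrast correlation (1 or 0.5) times the visit correlation (1 or ρ). Simulation with 1,000,000 draws, each test two-sided at 0.05, gives:

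| ρ | Any false rejection | False rejection favouring YLDJJ |
|---|---|---|
| 0 | 31.6% | 17.0% |
| 0.3 | 29.8% | 15.3% |
| 0.5 | 26.9% | 13.5% |
| 0.7 | 22.7% | 11.4% |
| 0.8 | 20.0% | 10.0% |
| 0.9 | 16.5% | 8.2% |

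The middle column compares with a nominal 5%, the right-hand column with 2.5% per test. The independence bound is 1 − 0.95⁸ = 33.7%. If correlation decays with distance between visits (lag-1 correlation 0.5 to 0.8), the two-sided figure is 28.4% to 22.1%. The model adjusts for baseline VAS, which lowers the relevant correlation: with a common raw correlation r, the residual one is r/(1 + r). Raw values of 0.5 to 0.8 become 0.33 to 0.44, and the error is 29.4% to 27.8%.

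**4. Remedies.**

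- *One visit, fixed sequence, each test at 0.05:* family-wise error is at most 5%, and power for the first contrast stays at 91.5%. The second can be claimed only if the first succeeds. If both true differences are 1.5, the chance that both succeed is at least 1 − 2 × (1 − 0.915) = 0.83. The same bound applies to a rule that both must succeed.
- *One visit, Holm:* the first step is at 0.025, where pairwise power with 33 completers per group is 86%. Sizing for 90% at 0.025 needs 38 per group; 38/0.8 = 47.5, so 48 per group and 144 in total.
- *All eight tests with Bonferroni (0.00625):* power with 33 completers per group is 71%.

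**The case against.** A reader might infer that the plan orders eight tests at 0.05 and that the error is simply 20–30%. The text does not support that. The Primary outcome analysis section estimates differences at each visit with confidence intervals, and separately tests two hypotheses that have no visit attached. Eight confirmatory tests is the most permissive reading. The 20–30% also rests on correlations that the article does not give, and it counts errors in both directions although the hypotheses are directional. These points stand, and the size is therefore given by reading.

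Three further defences are available.

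- **Day 20 is implied.** It is a condition for the per-protocol set, not a named endpoint of the intention-to-treat analysis. The Introduction stresses pain relief retained at 3 months, so a later visit could be argued equally well. Granting day 20 still leaves about 9%.
- **Both contrasts may be required.** The two hypotheses are joined by a plain conjunction, and the section speaks of testing against both controls. If success required both at one named visit, no adjustment would be needed. No such rule is stated, and neither is an either-one rule.
- **The analysis plan may settle it.** Testing order and alpha allocation often sit there, so the article's silence on those alone would be no fault. This does not cover the wording that points the primary analysis at every visit, because the time point is part of the outcome's definition.

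**Conclusion.** The point holds as a gap in the definition of the primary claim: no primary visit, and no multiplicity or decision rule for the two contrasts, while adjustment is stated only for secondary outcomes. Its size depends on the reading:

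- One visit primary, either contrast sufficient: about 9%.
- Any of the eight results sufficient: about 20–30% two-sided for between-visit correlations of 0.3–0.8, and 16.5% at 0.9. For false claims favouring YLDJJ this is about 10–15% against 2.5% per test.
- Both contrasts required at one named visit: no inflation, but the article does not say this.

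The lack of control follows from the text. The larger figures rest on assumed correlations and on the most permissive reading.

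**What to change.** Before unblinding:

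1. Name one primary visit. The end-of-treatment assessment already used in the per-protocol definition is the natural candidate, although a later visit could be defended.
2. First reconcile the two schedules in the experimental-group description. The text gives 20 sessions at five days per week over four weeks, while Table 2 gives 20 consecutive days for rTMS. On a five-day week starting on its first day, the twentieth session falls on calendar day 3 × 7 + 5 = 26. Day 20 and end of treatment must mean the same visit before either defines the endpoint.
3. Test the two contrasts at that visit in a pre-specified fixed sequence at two-sided 0.05 (for example sham first, then conventional acupuncture), or state that both must succeed.
4. Move the other visits to secondary, under the false discovery rate procedure already planned.

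The cost is protocol and analysis-plan wording and a registry update. The fixed sequence needs no added patients to hold the error and keep the power of the first contrast. The power to claim both should be stated. Other visits can no longer carry the primary claim. If Holm is chosen instead, restate the power: about 86% per contrast at the first step with 33 completers per group, below the stated 90%.

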### Secondary outcomes

#### Motor function recovery

Motor function recovery will be assessed using two measures. The Brunnstrom stages of recovery will be used to evaluate upper limb and hand function, ranging from Stage I (flaccidity) to Stage VI (near-normal coordination). The simplified Fugl-Meyer assessment (FMA) will be used to assess the motor function of the upper extremity, with scores ranging from 0 to 66 (higher scores indicating better function).

#### Muscle tone

Muscle tone will be assessed using the modified Ashworth scale (MAS), which measures resistance to passive movement. Scores will range from 0 (no increase in tone) to 4 (rigidity).

#### Shoulder mobility

Shoulder mobility will be evaluated using active range of motion (AROM) for flexion, extension, and abduction. A goniometer will be used, with a range of 0° to 180°. Higher degrees will be considered better mobility.

#### CRPS-specific severity

The CRPS severity score (CSS) will be used to comprehensively assess the cardinal features of CRPS-I (sensory, vasomotor, sudomotor, and motor/trophic changes) following the Budapest criteria, providing a disease-specific measure of severity (4).

#### Activities of daily living (ADL)

ADL will be assessed using the modified Barthel index (MBI), which covers domains such as feeding, dressing, toileting, continence, and mobility. Scores will range from 0 to 100, with higher scores indicating greater degrees of independence.

#### Thermal asymmetry

Thermal Asymmetry: Infrared thermography (FLIR E86) will be used to measure skin temperature at 3 regions (distal forearm, palm, and fingertips) of the affected and unaffected upper limbs. Thermal asymmetry is defined as ΔT ≥ 1.5 °C between homologous regions (39). To minimize confounding, measurements will be conducted in a temperature-controlled room (24 ± 1 °C) after a 20-min acclimatization period, during which the participants will rest in a seated position with both upper limbs exposed. Participants will be instructed to abstain from caffeine, smoking, and strenuous exercise for at least 2 h before assessment. Emotional state will be briefly recorded at the time of measurement.

#### Neuroplasticity correlates

Neuroplasticity correlates: Resting-state fMRI (3 T Siemens Prisma) will be analyzed using DPABI v6.0. Seed-based functional connectivity will focus on the anterior cingulate cortex (MNI coordinates: *x* = 0, *y* = 30, *z* = −10) and insula (*x* = 38, *y* = 20, *z* = −6), with connectivity strength calculated as Pearson’s correlation coefficients (29).

### Exploratory outcomes

#### Blinding

The success of blinding will be assessed using Bang’s blinding index (BI), which measures participants’ guesses of their group allocation at each time point.

#### Adverse events (AEs)

The safety profile will include AEs recorded following CTCAE v5.0. AE analysis will focus on incidence, severity, and causality (classified as definite, probable, or possible).

#### Rescue medication handling

The use of rescue medication (Celebrex) will be quantitatively recorded at each assessment session, incorporated as a covariate in linear mixed models to control confounding. It includes sensitivity analyses excluding high-frequency users (>3 doses/week).

#### Sample size

Sample size was calculated using G*Power 3.1.9.7 software (40), based on the primary outcome measure of pain intensity assessed by the VAS. Key parameters were set as follows: a minimum clinically important difference (MCID) of 1.5 points on the VAS, a standard deviation (SD) of 1.8 points derived from pilot data, a two-tailed significance level (*α*) of 0.05, and a statistical power (1 − *β*) of 90%. For the three-arm parallel design, which is meant to be analyzed using one-way analysis of variance (ANOVA), an effect size (f) of 0.42 (classified as Cohen’s medium-to-large effect) was estimated (25). The initial calculation indicated a requirement of 33 participants per group. To account for a conservative dropout rate of 20%, resulting in a final allocation of 42 participants per group (total *N* = 126).

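### The 33 per group does not follow from the stated three-arm ANOVA (f = 0.42 needs 25), and that ANOVA is not the planned primary analysis; the calculation is mislabelled rather than the trial shown to be underpowered

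*Protocol article*

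**What the plan says.** The protocol article's Sample size section says that the calculation was done in G*Power, "based on the primary outcome measure of pain intensity assessed by the VAS". The difference to detect is given as "a minimum clinically important difference (MCID) of 1.5 points on the VAS". For the spread, the section uses "a standard deviation (SD) of 1.8 points derived from pilot data". Alpha is 0.05 two-sided and power is 90%. It then describes a three-arm design "which is meant to be analyzed using one-way analysis of variance (ANOVA), an effect size (f) of 0.42", and gives a literature citation for that effect size. The result is reported as "The initial calculation indicated a requirement of 33 participants per group", raised to 42 per group (126 in total) for 20% dropout.

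The Primary outcome analysis section plans something else: "Pain intensity, measured based on the VAS, will be analyzed using a linear mixed-effects model (LMM"), followed by two pre-planned contrasts, experimental against sham and experimental against conventional acupuncture. It plans no omnibus test across the three arms. One-way ANOVA appears elsewhere only under Descriptive statistics, for baseline comparisons. The Software and reporting section states a multiplicity adjustment for secondary outcomes only.

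**The concern.** The paragraph gives every input that an ANOVA sample size needs, so a reader can repeat it, and the repeat does not return 33. The effect size also does not follow in any obvious way from the difference and SD listed beside it. Finally, the test that was sized is not the test on which the trial will draw its conclusion.

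What is at stake is the meaning of the 90%. As written, it belongs to an omnibus test that is not planned. The reader is not told the power of the comparison with sham, of the comparison with conventional acupuncture, or of both succeeding.

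**Working it through.** **Inputs from the Sample size section:** difference 1.5, SD 1.8, alpha 0.05 two-sided, power 90%, k = 3 groups, f = 0.42, dropout 20%.

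**1. The plan's own figure.** The ANOVA power is P(F′ > F crit), where F′ is noncentral F with k − 1 and N − k degrees of freedom and noncentrality λ = N·f².

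| n per group | λ = 3n × 0.42² | Power |
|---|---|---|
| 24 | 12.70 | 88.7% |
| 25 | 13.23 | 90.1% |
| 33 | 17.46 | 96.6% |

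The requirement is 25 per group (75 in total), against the stated 33 (99 in total). Changing alpha or power does not recover 33 at f = 0.42: 95% power gives 31, alpha 0.025 gives 30, and alpha 0.05/3 gives 32. None of these variants is what the paragraph states.

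**2. The dropout step.** 33/0.8 = 41.25, rounded up to 42; 42 × 3 = 126. This step reproduces.

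**3. From the difference and SD to f.** d = 1.5/1.8 = 0.833. If 1.5 is the largest difference among three arms:

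- middle arm halfway: f = d·√(1/6) = 0.340
- two arms equal and one 1.5 apart: f = d·√8/6 = 0.393

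| f | n per group for 90% | Power at 33 per group |
|---|---|---|
| 0.340 | 38 | 85.6% |
| 0.393 | 29 | 94.1% |

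The stated 0.42 lies above this range. The two-group conversion is d/2 = 0.417, which rounds to 0.42.

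**4. Where 33 may come from.** A two-sample t-test with d = 0.833, two-sided 0.05 and 90% power needs 32 per group (31 gives 89.8%, 32 gives 90.7%). The normal approximation gives 31. The stated 33 is within two of both.

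**5. Power of the planned contrasts at 33 evaluable per group.** The true difference is taken as 1.5 in both contrasts and the SD as 1.8. Single-contrast figures are from noncentral t with noncentrality d·√(33/2) = 3.385. The figures for both contrasts are from simulation, 400,000 runs with pooled SD.

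| Quantity | Power |
|---|---|
| One contrast, alpha 0.05 | 91.5% |
| One contrast, alpha 0.025 | 85.9% |
| Both contrasts, 0.05 each | about 86% |
| Both contrasts, 0.025 each | about 78% |

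**6. Smaller advantages over conventional acupuncture.** The protocol states no difference other than 1.5, so these values are assumptions. At alpha 0.05 and 33 per group, true differences of 0.5, 0.75 and 1.0 points give about 20%, 38% and 60% power.

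**The case against.** Four points can be made for the protocol.

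- **The source of f.** The minimum important difference is a minimum, so 1.5 need not be the largest gap between arms. Means of 0, 1.5 and 1.7 with SD 1.8 give f = 0.421. The effect size is also attributed to a cited study. This stands. A reader might infer that 0.42 is impossible with these inputs, but that holds only if 1.5 is the largest between-arm difference. The match with d/2 is a likely explanation, not a proof. None of this affects the result of 25, which takes f = 0.42 as given.
- **The 90% and the contrasts.** A reader might infer that no planned contrast could have 90% power once multiplicity is controlled. That is not so. In a fixed sequence, the contrast tested first keeps alpha 0.05 and has 91.5%. The shortfall appears with an equal alpha split, or when both contrasts must succeed.
- **A simpler test for sizing.** Sizing on a simpler test than the final model is common, and adjustment for baseline VAS can add precision. If 1.8 is an unadjusted SD (the protocol does not say) and the baseline correlation were 0.4 (assumed), dividing d by √(1 − 0.4²) gives about 95% power at 0.05 and 92% at 0.025. This stands as a reason not to call the trial too small. It does not justify sizing on a three-group omnibus test when the hypotheses are two pairwise contrasts.
- **The size of the advantage over conventional acupuncture.** Whether 1.5 points is optimistic against an active comparator is a design judgement and not an arithmetic error. That also stands, so the figures for smaller differences are illustrations only.

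**Conclusion.** The sample-size statement is wrong as written on two counts. Its own ANOVA inputs give 25 per group and not 33, and the ANOVA is not the planned primary analysis. That f = 0.42 does not match 1.5 and 1.8 is a third, conditional point: it assumes that 1.5 is the largest between-arm difference.

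A reader might infer that the trial is underpowered, or that it could be cut to 25 per group. The documents support neither. The stated 33 exceeds the 25 that the named ANOVA needs, and the 32 that one pairwise comparison needs on the stated difference, SD, alpha and power. Cutting to 25 would rest on an effect size and a test that do not match the planned contrasts. The most plausible reading is a two-group calculation labelled as a three-group ANOVA.

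The contrast figures assume 33 evaluable participants per group, a common SD of 1.8, a true difference of 1.5 in each contrast, and a single time point. They take no credit for baseline adjustment.

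**What to change.** Keep N = 126. Remove the ANOVA and f = 0.42 as the basis of the calculation, or justify f separately by stating the pattern of arm means and the source behind it, and correct the n that follows. Restate the calculation for the two planned contrasts at a named time point: difference 1.5, SD 1.8, 33 evaluable per group, with the alpha for each contrast. Say whether 1.8 is the SD of scores or of changes, and whether it is adjusted for baseline.

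Report the power that goes with the chosen testing rule:

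- about 91.5% per contrast at two-sided 0.05
- about 86% for winning both at 0.05 each, for example in a fixed sequence
- about 86% per contrast if alpha is split to 0.025

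Optionally, add the power against conventional acupuncture at 0.5, 0.75 and 1.0 points (about 20%, 38% and 60%), labelled as assumptions.

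The cost is a rewritten paragraph. Recruitment and N do not change, and the primary model stays as planned. The team has to name the time point and the alpha rule that the power statement refers to.
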